### Safety Considerations

All AEs or serious adverse events (SAEs) will be monitored and collected throughout this study’s period. SAEs include any serious incidents resulting in death, persistent or significant disability or incapacity, requiring (extension of) hospitalization, or life-threatening situations. AEs include any nonserious incidents regarding the health and well-being of the participant, related or unrelated to trial participation, as well as technical problems with the hardware (ie, study smartphone), software (ie, smartphone app and assessments), and training used in this trial. SAEs are not expected to occur as a result of the intervention or study participation. If occurring, SAEs will be reported to this trial’s steering committee (TSC) and ethics and data advisory board (EDAB), which can advise on ethical concerns and monitor evidence for intervention harm. At the end of this trial, SAE will be reported to the local ethics committee. AE and SAE will be reported in publications of this study’s results. Insurance is in place for participants who endure harm through their participation in this study.

### Statistical Analysis

#### Feasibility

All statistical analyses will be performed using Stata 17 (StataCorp LLC). To address the objectives of establishing the feasibility of this trial’s methodology and delivery of the CliMACT training, descriptive statistics will be used (mean, SD, n, %). Evaluation of meeting important feasibility criteria will be based on a traffic light system with 3 categories, with green indicating that full feasibility is established, yellow indicating that feasibility is established, but study procedures need to be modified, and red indicating that feasibility is not established. Feasibility of trial methodology (objective 1) will be based on recruitment, randomization, and retention, and evaluated according to a priori determined cutoffs shown in Table 1, with the primary objective of establishing the feasibility of recruitment for a future efficacy-effectiveness RCT (that informed our justification of the sample size, see above). Feasibility of delivering the CliMACT training (objective 2) will be based on participant satisfaction, participant adherence, and mental health professional fidelity to the training protocol, and will also be evaluated according to predetermined cutoffs (Table 1).

**Table 1 table1:** Traffic light criteria for the feasibility of trial methodology and the feasibility of delivering the CliMACT^a^ training.

			Green		Yellow		Red
**Feasibility of trial methodology**							
	Recruitment	Monthly recruitment rate of n=11 to n=17 participants in (at least) the month with the highest recruitment rate during the feasibility RCT^b^ recruitment period		Monthly recruitment rate of n=5 to n=10 participants in (at least) the month with the highest recruitment rate during the feasibility RCT recruitment period; recruitment area should be opened to places outside Mannheim and Rhine-Neckar		A monthly recruitment of n<5 participants for all months of the feasibility RCT recruitment period	
	Randomization	Successful randomization of n=10 to n=17 participants in (at least) the month with the highest randomization rate during the feasibility RCT recruitment period		Successful randomization of n=4 to n=9 participants in (at least) the month with the highest randomization rate of the feasibility RCT recruitment period		Successful randomization of <4 participants in all months of the feasibility RCT recruitment period	
	Retention	Retention rate of at least 85% of all randomized participants, for outcome assessment of at least one of the assessment time points at posttraining and 4-week follow-up		Retention rate of at least 75% for outcome assessment of at least one of the assessment time points at posttraining and 4-week follow-up		<75% retention at both posttraining and 4-week follow-up	
**Feasibility of delivering the CliMACT training**							
	Participants satisfaction with the training	Moderate to high satisfaction in general in a debriefing questionnaire (mean score of ≥4 on a 7-point scale) and the global star-rating of the Mobile Application Rating Scale (mean rating of ≥3 on a 5-point scale)		Fair satisfaction in general in a debriefing questionnaire (mean rating of >3 and <4) and the global star-rating of the Mobile Application Rating Scale (mean rating of >2 and ≤3). Adjustment and optimization of the training or app are required		Low satisfaction in general in the debriefing questionnaire (mean rating ≤3) and the global star-rating of the Mobile Application Rating Scale (mean rating ≤2)	
	Participant adherence to intervention protocol	Moderate to strong adherence to training sessions (at least 80% of participants attending at least 2 of the 3 face-to-face sessions) and EMI^c^ components (mean of ≥1 consolidating or adaptive EMI components completed per week)		Fair adherence to training sessions (at least 60% of participants attending at least 2 of the 3 face-to-face sessions) and EMI components (mean of 0.8 consolidating or adaptive EMI components completed per week). Adjustment and optimization of sessions or the app are required		Poor adherence to training sessions (<60% of participants completing at least 2 of the 3 face-to-face sessions) and EMI components (mean of <0.8 consolidating or adaptive EMI components per week)	
	Mental health professional fidelity to training protocol	Moderate to high fidelity to intervention protocol (≥80% of core components delivered by trained psychologist) and use of ACT^d^-consistent skills (mean rating of ≥1.5 on a 4-point scale ranging from 0-3)		Fair fidelity to intervention protocol (≥60% of core components delivered by trained psychologist) and use of ACT-consistent skills (mean rating of >1 and <1.5 on a 4-point scale ranging from 0-3). Adjustment of sessions, EMI app, or training of psychologists is required		Poor fidelity to intervention protocol (<60% of core components delivered) and use of ACT-consistent skills (mean rating of <1 on a 4-point scale ranging from 0-3)	

^a^CliMACT: Climate Mind and Act.

^b^RCT: randomized controlled trial.

^c^EMI: ecological momentary intervention.

^d^ACT: acceptance and commitment therapy.

As nonspecific active ingredients (objective 2 continued), we will explore the association of working alliance toward mental health professionals as well as working alliance with the app-based EMI with the 8 candidate outcomes in participants of the experimental condition, using linear mixed models. Separate models will be fitted for each alliance type and candidate outcome at both posttraining and 4-week follow-up; additionally, time (posttraining and 4-week follow-up), the respective outcome at baseline, and working alliance will be entered as independent variables (details set in preregistered statistical analysis plan, becoming public on OSF after publication of results) [87]. A level-2 random intercept for subject and a random effect for time will be added, and level-1 residuals will be allowed to be correlated to account for within-subject nesting of repeated measures. For the 2 momentary outcomes of nonspecific active ingredients, outcomes measured at baseline will be person-mean centered, and, in addition to the above specifications, random slopes for time and working alliance will be added, with an unstructured variance-covariance matrix. Within-subject residuals will be modeled with an autoregressive structure of the exponential type, allowing the models to account for unequally spaced time values. Restricted maximum likelihood estimation will be applied.

As specific active ingredients (objective 2 continued), we will explore proximal effects of CFI-based CliMACT training components on momentary negative affect in an MRT design in participants in the experimental condition using linear mixed modeling. MRT condition (experimental: any adaptive CFI-based training component vs control: no adaptive training component, randomized at a ratio of 6:1 in moments of higher negative affect), negative affect at *t*_n_ (person-mean centered), and time between assessment time points will be entered as independent variables. Negative affect at *t*_n+1_ will be entered as the dependent variable. A level-2 random intercept will be added, and level-1 residuals will be allowed to be correlated to account for within-subject nesting of repeated measures. Restricted maximum likelihood estimation will be applied.

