### Justification of Sample Size

#### Feasibility RCT

The sample size for this feasibility RCT is primarily determined to address the primary objective to provide the basis for successful recruitment in a fully powered efficacy-effectiveness RCT. Initial sample size planning points to ≈180 participants required for the full RCT. To this end, we set a feasibility limit of a minimum monthly recruitment rate of 11 participants in (at least) the month with the highest recruitment rate of the feasibility trial recruitment period. This lower bound reflects the minimum monthly recruitment rate required to recruit an expected ≈180 participants for a subsequent fully powered RCT within a designated period of 17 months. This study’s population for the feasibility RCT will comprise a maximum of 50 youth aged 14-25 years (n=25 in the experimental and control conditions, respectively) with climate change–related distress. This upper limit of 50 is based on recommendations by Whitehead et al [84] for determining sample size for feasibility RCTs and would reflect a monthly recruitment rate of 17 if recruitment can be completed within 3 months. Thus, the feasibility trial will inform us about the feasibility of the aspired recruitment rate and the possibility of overrecruitment.

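### Table 1 gives no colour to mixed results on satisfaction, adherence and fidelity, never turns red on one failed component, and has faulty band edges

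*Protocol article*

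**What the plan says.** The Feasibility subsection of the Statistical Analysis sets up a three-colour system. Green means full feasibility, yellow means feasible with changes, and the definition ends with "red indicating that feasibility is not established". The cutoffs in Table 1 are described as fixed in advance.

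In the delivery half of Table 1, each criterion has two measures joined by *and* in every colour:

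- **Satisfaction:** debriefing mean (green ≥4, yellow >3 and <4, red ≤3) and star rating. The green star cut is "mean rating of ≥3 on a 5-point scale". Yellow is "the global star-rating of the Mobile Application Rating Scale (mean rating of >2 and ≤3", and red is ≤2.
- **Adherence:** share of participants attending at least 2 of 3 sessions (green at least 80%, yellow at least 60%, red <60%) and mean EMI components per week (green ≥1, yellow 0.8, red <0.8). The red cell begins "Poor adherence to training sessions (<60% of participants completing at least 2 of the 3 face-to-face sessions) and EMI components".
- **Fidelity:** core components delivered (green ≥80%, yellow ≥60%, red <60%) and ACT-consistent skills (green ≥1.5, red <1). Yellow for ACT skills is "mean rating of >1 and <1.5 on a 4-point scale ranging from 0-3".

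The table gives no rule for a result whose two measures fall in different colours.

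For retention, green is "Retention rate of at least 85% of all randomized participants, for outcome assessment of at least one of the assessment time points". Yellow uses the same form at 75%, and red requires less than 75% at both time points. The planned sample is "a maximum of 50 youth aged 14-25 years (n=25 in the experimental and control conditions, respectively").

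**The concern.** A traffic-light rule fixed in advance is useful only if every possible result maps to one colour. Here a trial that does well on one measure and poorly on the other, which is an ordinary outcome, falls outside all three cells. The team would then have to choose the colour after seeing the data, which is what fixing cutoffs in advance is meant to prevent. Because red needs both measures to fail, a clear failure on one of them is never labelled as such. The Discussion makes the fully powered trial depend on feasibility being established, so the label matters.

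**Working it through.** **Figures behind the table.** The recruitment cutoffs reproduce. The lower bound is the rate "required to recruit an expected ≈180 participants for a subsequent fully powered RCT within a designated period of 17 months": 180/17 = 10.59, rounded up to 11 a month. The upper bound is 50 participants in 3 months: 50/3 = 16.67, rounded up to 17. Recruitment and randomization each have one measure, and their red, yellow and green bands adjoin. The fault lies in the two-measure criteria.

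**Colour pairs.** Each measure can be green (G), yellow (Y) or red (R), so each criterion has 3 × 3 = 9 pairs. To favour the plan, *at least 60%* is read as including values above 80%, and the yellow EMI value 0.8 is read as ≥0.8.

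| Criterion (first measure, second measure) | Pairs with a colour | Pairs without |
|---|---|---|
| Satisfaction (debriefing, stars) | GG, YY, RR | 9 − 3 = 6 |
| Adherence (sessions, EMI) | GG, GY, YG, YY, RR | 9 − 5 = 4 |
| Fidelity (core, ACT) | GG, GY, YY, RR | 9 − 4 = 5 |

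In fidelity, YG has no colour because the yellow ACT band stops below 1.5.

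**Share of possible results.** The cells were also coded literally on a grid: 0.1 steps on the scales and on EMI components from 0 to 2 a week, k/25 for sessions, and 1% steps for core components. Results without a colour were:

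- satisfaction: 1529/2501 = 61%
- adherence: 349/546 = 64%, or 283/546 = 52% with 0.8 read as ≥0.8
- fidelity: 2031/3131 = 65%

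These are shares of a grid, not probabilities.

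**Examples without a colour.**

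- Sessions 10/25 = 40% with 1.5 EMI components a week: sessions red, EMI green.
- Sessions 22/25 = 88% with 0.3 EMI components a week: sessions green, EMI red.
- Debriefing 5 with stars 2: debriefing green, stars red.
- Core components 70% with ACT 2.0: core yellow, ACT green.

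The first three contain a failed component and none is red.

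**Band edges.**

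- Stars = 3: 3 ≥ 3 is green, and 2 < 3 ≤ 3 is yellow.
- ACT = 1: 1 > 1 is false, so not yellow. 1 < 1 is false, so not red.
- EMI = 0.9: not ≥1, not equal to 0.8, not <0.8. The interval between 0.8 and 1 is uncovered.

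**Effect of taking the worse colour.** On the same grids, with the edges closed as set out in the fix, every result that now has a single colour keeps it. Every result without a colour becomes red or yellow, and none becomes green. On the cumulative adherence reading, results that meet both green and yellow become green.

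**Retention.** With n = 50, 85% needs 43 participants (0.85 × 50 = 42.5) and 75% needs 38 (0.75 × 50 = 37.5). Retention of 43/50 = 86% post training and 30/50 = 60% at follow-up is green, because one time point suffices.

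**The case against.** **Other readings of the cells.** They could be meant as a list of cutoffs, one per component. The yellow remedies point that way, since they name sessions or app, or the training of psychologists, as alternatives. On that reading red would not require both to fail. The rule for combining the components would still be missing, so the gap stands. The preregistered analysis plan is not shown and may contain such a rule, but the article presents the Table 1 cutoffs as already determined.

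**Size of the edge faults.** These are slips. The star overlap gives no double colour for the criterion, because green needs a debriefing mean of at least 4 and yellow needs one below 4. The ACT gap needs a mean of exactly 1. The EMI gap covers a range and matters more.

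**Stronger readings to avoid.** A reader might infer that a poor delivery result could be declared green. It cannot, because green needs both components. Nor is a result without a colour a pass: it meets neither of the two colours that establish feasibility. The article also states no mechanical go/no-go step, since findings are to be discussed with the advisory group.

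**Retention.** A reader might infer that the one-time-point rule is an error that yields a false green. The rule is explicit and internally consistent. The Measures section says retention is assessed at both visits but sets no pass rule there. The mixed model still uses participants seen at only one visit. Requiring 85% at both visits would be severe: with true retention of 85% at each, n = 50 and an assumed latent correlation of 0 to 0.8, green would occur in about 27% to 37% of trials. This is a trade-off, not a contradiction.

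**Conclusion.** The concern holds for satisfaction, adherence and fidelity. As written, 6, 4 and 5 of 9 colour pairs have no colour, and failure of one component alone never yields red. The counts rest on reading *and* as a conjunction. For adherence and fidelity they also rest on reading the yellow lower limits cumulatively, and for adherence on taking 0.8 as ≥0.8. Without that last allowance the adherence gap is wider. The three edge faults follow directly from the inequality signs. The consequence is an undefined label or a missed red, not a wrongly awarded green.

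The retention rule is lenient, and a green at one visit can hide a shortfall at the other. That calls for fuller reporting, not a new cutoff. Recruitment, which the article names as the primary objective, is not affected.

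**What to change.** 1. State in Table 1 that each component is coloured separately and that the criterion takes the worse colour.
2. Close the edges: star-rating yellow >2 and <3, EMI yellow ≥0.8 and <1, ACT red ≤1.
3. The Results section gives 25 August 2025 as the end of data collection, so date this clarification before the criteria are summarised. If they have already been summarised, declare the colouring rule post hoc and report every component with its own colour.
4. Keep the retention rule. Beside its colour, report retention at post training and at 4-week follow-up against the 85% and 75% limits.

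The cost is a wording change, with no further participants or data. The downside is small: some results that now have no colour will become red or yellow.

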#### Feasibility of Delivering the CliMACT Training

The feasibility of delivering the CliMACT training will be assessed at the posttraining assessment based on the criteria as delineated in the following. Satisfaction is measured through 3 scales. A 21-item participant debriefing questionnaire with a 7-point Likert scale ranging from 1-7, with higher values indicating higher satisfaction [16]. The 6-item perceived impact subscale of the Mobile App Rating Scale has a 6-point scale ranging from 0-5, with higher scores indicating higher perceived helpfulness. Lastly, there will be one item reflecting a global 5-star rating of the application, ranging from 1-5 [44].

Participant adherence is measured using the number of attended sessions and the number of completed consolidating and adaptive EMI components during training.

Fidelity to the training protocol is measured using a 19-item session component checklist adapted to CliMACT training components from the study by Reininghaus et al [16] with a yes-no format, and the 25-item Acceptance and Commitment Therapy Fidelity Measure with a 4-point scale ranging from 0-3 [45], with higher values indicating greater frequency of behavior aligned with ACT principles. Measures are completed by the mental health professional delivering the face-to-face session and by an independent rater. As active ingredients, CliMACT training components will be assessed as specific ingredients, and working alliance with the mental health professional and with the digital tool are measured as nonspecific ingredients, using the 12-item Working Alliance Inventory with a 5-point Likert scale ranging from 1-5 (Working Alliance Inventory-Self Report [WAI-SR]) [46,47] and 25-item Mobile Agnew Relationship Measure with a 7-point Likert scale ranging from 1-7 [48], with higher scores indicating a more positive working alliance for both measures.

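### The alliance models for the two momentary outcomes give working alliance a participant-level random slope, although each participant has only one alliance value

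*Protocol article*

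**What the plan says.** The model is set out in the protocol article, Statistical Analysis, Feasibility subsection, in the first paragraph after Table 1. The association of alliance with the candidate outcomes is examined "in participants of the experimental condition, using linear mixed models", with a separate model per alliance type and outcome. The base specification reads "A level-2 random intercept for subject and a random effect for time will be added". For the two momentary outcomes it is extended: "random slopes for time and working alliance will be added, with an unstructured variance-covariance matrix". Estimation is by REML.

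The timing of the alliance measures comes from Measures, Feasibility of Delivering the CliMACT Training. That section opens with "The feasibility of delivering the CliMACT training will be assessed at the posttraining assessment" and later states that "working alliance with the mental health professional and with the digital tool are measured as nonspecific ingredients". It gives no per-session or follow-up alliance measurement. The planned sample is "n=25 in the experimental and control conditions, respectively".

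**The concern.** A random slope by participant describes how the effect of a predictor differs from one participant to the next. To estimate it, the predictor must take different values within a participant. If alliance is recorded once, every momentary report of a participant, at posttraining and at follow-up, carries the same alliance value. More prompts or more waves do not change that.

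Software may still return a number for the slope variance, because alliance differs between people. That number describes unequal between-person variance, not person-specific alliance effects, and could be misread as the latter. It also sets the weights and the standard error of the fixed alliance coefficient, which is what this part of objective 2 is after. The protocol announces 95% CIs and d-type effect sizes as what will be read from its exploratory analyses, so an interval that is too narrow is a defect in the main output of these models. Four models are affected: 2 momentary outcomes × 2 alliance types.

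**Working it through.** The protocol gives no power or precision figure for the alliance models, so there is none to reproduce. The check has an algebraic part, which needs no assumptions, and a simulation part, which does.

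**Inputs from the protocol**
- Participants: 25 in the experimental arm. Table 1's green retention criterion, "Retention rate of at least 85% of all randomized participants", gives 0.85 × 25 = 21.25, so about 21.
- Outcome waves: 2 (posttraining, 4-week follow-up).
- Momentary reports per wave: 8 per day × 6 days = 48 scheduled.
- Estimation: REML, unstructured random-effects covariance.

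**Inputs assumed (not in the protocol)**
- 29 completed reports per wave (29/48 = 60%).
- Alliance W approximately normal, mean 3.8, SD 0.7, clipped to 1–5.
- Intercept variance 1.0, time-slope variance 0.3, correlation −0.2, residual variance 1.5, independent residuals.
- True alliance effect 0; true alliance-slope variance 0 unless stated.

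**Step 1: what the term does.** Let the random effects be intercept (0), time (t) and alliance (w), with covariance elements g. For two reports of one participant at times s and t, the covariance from the random effects is

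`(g00 + 2·g0w·W + gww·W²) + (s + t)·(g0t + gtw·W) + s·t·gtt`

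W is a constant for that participant. The columns [1, W] have rank 1 within a person, so their block is `(g00 + 2·g0w·W + gww·W²)` times a matrix of ones (confirmed numerically, maximum difference 9 × 10⁻¹⁶). The covariance matrix grows from 2·3/2 = 3 to 3·4/2 = 6 parameters. The three added ones only make the intercept variance quadratic in W and the intercept–time covariance linear in W. They are informed solely by how the spread between at most 25 people changes with alliance.

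**Step 2: consequence for the alliance coefficient.** 1,500 data sets per scenario, each fitted without and with the alliance slope:

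| n | Alliance slope | Empirical SD | Mean SE | Coverage, Wald | Coverage, t (n − 3 df) |
|---|---|---|---|---|---|
| 25 | no | 0.336 | 0.305 | 90.8% | 92.2% |
| 25 | yes | 0.389 | 0.308 | 86.7% | 88.5% |
| 21 | no | 0.363 | 0.334 | 91.8% | 93.7% |
| 21 | yes | 0.439 | 0.338 | 85.5% | 88.1% |

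Ratios of empirical SD: 0.389/0.336 = 1.16 and 0.439/0.363 = 1.21. Ratios of mean SE: 0.308/0.305 = 1.01 and 0.338/0.334 = 1.01. The Monte Carlo standard error of a coverage figure is about √(0.867 × 0.133 / 1500) = 0.9 percentage points. At n = 25 the median fitted slope variance was 0.36 (5th to 95th percentile 0.03 to 2.26) although the truth was 0; only 1.9% of runs fell below 0.01. Centring W made no material difference.

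**Step 3: a case chosen to favour the slope.** With between-person spread that really varies with alliance (0.5 SD per alliance point), the slope still did not help. At n = 25 the SD went from 0.370 to 0.413 and Wald coverage from 90.5% to 86.8%. At n = 21 the SD went from 0.419 to 0.479 and coverage from 89.2% to 85.5%.

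**Step 4: a simpler model, to see how far the size depends on assumptions.** Participant means were regressed on alliance, person variance 1, t limits, other terms left out. With error variance of the participant mean 0.05 (3,000 runs), coverage fell from 95.1% to 91.5% (n = 21) and from 94.4% to 92.0% (n = 25). The empirical SD went from 0.362 to 0.415 and from 0.329 to 0.364, that is, ratios of 1.15 and 1.11. The mean SE was almost unchanged (0.348 to 0.350; 0.317 to 0.318). Varying the error variance at n = 21, in two separate sets of runs, gave coverage without → with the slope:

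| Error variance | 800 runs | 500 runs |
|---|---|---|
| 0.05 | 94.8% → 89.5% | 95.2% → 90.2% |
| 0.25 | 95.0% → 93.1% | 95.8% → 94.0% |
| 0.50 | 96.8% → 95.4% | 95.6% → 93.4% |
| 1.00 | 96.6% → 96.1% | not run |

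The empirical SD rose by about 8–16% across the first set and 13–17% across the second; in the second set the mean SE rose by only 1–3%. For scale, the Step 2 assumptions give a one-wave mean an error variance of 1.5/29 = 0.052. A value of 0.25 would need a residual variance of 0.25 × 29 = 7.25 times the person variance with independent residuals, or strong autocorrelation.

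**The case against.** **The timing is inferred.** The opening sentence of the measures section speaks of assessing feasibility, and alliance is introduced later, as an active ingredient, without a timing of its own. Some measures in that section are plainly gathered during training (adherence, session fidelity). The schedule of measures (Figure 2), which lists both alliance instruments in its abbreviations, is not available here. This stands as a caveat: repeated measurement cannot be excluded. But the text states none. Alliance recorded at each of the three sessions would not by itself help either, because the modelled outcomes lie after training; alliance would have to be measured at follow-up as well to vary across those records.

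**The size depends on assumed variances.** This also stands. With much less precise participant means the undercoverage is small or absent, as Step 4 shows. The loss of precision appears in every scenario run and is the sturdier result.

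**Part of the undercoverage has another cause.** In the fuller simulation the model without the slope reaches only 90.8–91.8% with Wald limits. That part is small-sample inference and is not cured by removing the slope. The slope accounts for a further 4 to 6 points.

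**The stakes are limited.** The models are exploratory, alliance enters no traffic-light criterion, and selection of the later primary outcome rests on efficacy effect sizes. This bears on priority, not on whether the term is right.

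**Details are left to the analysis plan.** The article does refer to a preregistered plan, but it states this random slope itself. The point concerns a stated term, not an omission.

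**Conclusion.** The concern holds. On the protocol's text, alliance has one value per participant, and the random slope for it cannot represent what a random slope is meant to represent. The algebra depends on nothing except that timing. The practical effect is an alliance coefficient roughly 8–21% more variable, with a standard error that barely reflects this. The accompanying loss of 95% CI coverage is about 4 to 6 points in the fuller simulation (Wald limits) and ranges from about 5 points down to less than 1 in the simpler one, depending on how precise participant means are. The sizes rest on assumed variances, an assumed alliance distribution and, in the fuller simulation, assumed compliance; the protocol's exponential autoregressive residual was not simulated, though it cannot create within-person variation in alliance. The term should be corrected, but feasibility conclusions do not depend on it.

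**What to change.** In the Feasibility subsection of Statistical Analysis, delete the alliance term (three words) from the random slopes for the two momentary outcomes, and make the same change in the matching line of the analysis plan. Keep alliance as a fixed, between-person predictor with the random intercept for participant and the random effect for time.

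Two additions are worthwhile. State explicitly when each alliance measure is taken; if either was measured at more than one outcome wave, say so and define how it enters as a time-varying predictor. Use small-sample degrees of freedom (for example Satterthwaite or Kenward–Roger) for the alliance coefficient, since dropping the slope alone does not bring Wald intervals to nominal coverage with 21 to 25 participants.

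The cost is a short text edit, documented as a correction before the alliance models are interpreted. If alliance was measured once, no estimable quantity is lost, and data collection is unaffected.

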#### MRT Sample Size Calculation

To address the objective of exploring CliMACT training components as specific active ingredients, an MRT will be conducted. Based on the power approximation for MRTs [85,86], a sample size of 25 participants is sufficient to detect a small effect size of *d* ≥0.15 on a proximal EMA outcome, with *t*=252 decision points (based on our EMIs with a training duration of 42 days with 6 random EMA prompts per day) and a power of 80% for a 2-sided test α=.05, with an availability rate η (ie, proportion of completed EMA observations at given decision point T) of 50% and a randomization probability of 0.85 (ie, a ratio of 6:1 for experimental vs control components).

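### The 80% power stated for the microrandomized trial assumes an outcome after essentially every completed prompt, and the protocol does not say which next assessment supplies that outcome

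*Protocol article*

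**What the plan says.** Under Justification of Sample Size, MRT Sample Size Calculation, the protocol article states that "a sample size of 25 participants is sufficient to detect a small effect size of *d* ≥0.15 on a proximal EMA outcome", at "a power of 80% for a 2-sided test α=.05". The decision points are the EMA prompts of the training phase: 42 days with 6 prompts a day give 252. Availability is set at 50% and defined as the "proportion of completed EMA observations at given decision point". The randomization probability is 0.85, described as a 6:1 ratio.

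Under Statistical Analysis, Feasibility, the paragraph on specific active ingredients describes the MRT model. Its predictors are MRT condition, negative affect at t_n and the lag: "time between assessment time points will be entered as independent variables". On the outcome it says: "Negative affect at *t*_n+1_ will be entered as the dependent variable". It does not say whether t_n+1 is the next scheduled prompt or the next one the participant answers.

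**The concern.** A randomized moment informs the MRT contrast only if two things happen. The participant must answer prompt n, because randomization is triggered by that answer. Negative affect must also be recorded at t_n+1. The power statement discounts for the first and has no term for the second, although both assessments come from a prompt series for which the protocol expects only half the prompts to be answered.

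At stake is how an MRT result would be read. The Discussion lists the MRT among the design's strengths. If a null result were set against an 80% power figure that the number of usable pairs does not support, the adaptive components could be judged inactive too readily.

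**Working it through.** **Inputs stated in the MRT sample size section:** N=25, T=252, d=0.15, η=0.50, ρ=0.85 (an exact 6:1 ratio is 6/7=0.857), two-sided α=0.05.

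**Input not stated:** c, the probability that t_n+1 is observed given that prompt n was completed. The values of c below are assumptions. c=50% is the case where adjacent prompts are completed independently at the protocol's own rate.

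**Method.** Standard MRT power approximation with a constant proximal effect (assumed, because the protocol does not give the effect's shape over time). The noncentrality is λ = N·T·η·c·ρ(1−ρ)·d², and power is the upper tail of a noncentral F with 1 and N−2=23 degrees of freedom beyond the 5% critical value.

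**Step 1: reproduce the stated figure (c=1).** Completed prompts: 25 × 252 × 0.50 = 3150.
- ρ=0.85: λ = 3150 × 0.85 × 0.15 × 0.0225 = 9.04, power 0.821.
- ρ=6/7: λ = 3150 × (6/7) × (1/7) × 0.0225 = 8.68, power 0.805.

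So 25 participants and 80% power follow from the stated inputs when all 3150 completed prompts have an outcome.

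**Step 2: find the margin.** Solving for power 0.80 gives c of about 0.95 at ρ=0.85 and about 0.99 at ρ=6/7. A simpler normal approximation (0.852 at c=1, ρ=0.85) puts the crossing at about 0.87.

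**Step 3: take t_n+1 as the next scheduled prompt and vary c.** With N and the degrees of freedom fixed, the detectable d scales as 0.146/√c at ρ=0.85, where 0.146 is the value at c=1.

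| c | usable pairs | λ (ρ=0.85) | power, ρ=0.85 | power, ρ=6/7 | d at 80% power, ρ=0.85 |
|---|---|---|---|---|---|
| 100% | 3150 | 9.04 | 0.82 | 0.81 | 0.146 |
| 80% | 2520 | 7.23 | 0.73 | 0.71 | 0.163 |
| 70% | 2205 | 6.33 | 0.67 | 0.66 | 0.174 |
| 60% | 1890 | 5.42 | 0.61 | 0.59 | 0.188 |
| 50% | 1575 | 4.52 | 0.53 | 0.51 | 0.206 |

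At c=50% and ρ=0.85, 46 participants would be needed for 80% power at d=0.15.

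**Step 4: an intermediate reading.** Suppose t_n+1 is the next completed prompt on the same day, with six prompts each answered independently at 50%. The share of moments with an outcome is (0.96875 + 0.9375 + 0.875 + 0.75 + 0.5 + 0)/6 = 0.67, and power is about 0.66 (ρ=0.85).

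**Step 5: what these figures leave out.** They treat every completed prompt as randomized. Under Adaptive EMI Delivery Scheme and Randomization and Blinding, only moments above a negative-affect threshold are randomized. The powers above are therefore upper limits for each c.

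**The case against.** The strongest reply is that t_n+1 may mean the next completed assessment, whatever the lag. The model contains the time between assessments, which fits that reading. Almost every randomized moment would then have an outcome and this discount on the 80% would largely disappear. This stands as a possible reading. It is not established, because prompts sent at random times are unequally spaced anyway and a lag covariate is just as natural for consecutive scheduled prompts. It also has a cost: the effect would be measured at longer and variable lags, some of them overnight, rather than at the next prompt.

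A second reply is that completion clusters within persons and days, so fewer than half of the outcomes would be lost. That is fair. The 50% row is an independence case and not a prediction. Clustering moves power up the table, but it would have to bring next-prompt completion to about 95% to restore 80%.

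A reader might infer that the stated power is simply miscalculated, or that it cannot follow from the design. The documents support neither. The stated inputs reproduce the stated power, and the shortfall depends on an undefined t_n+1 and on a completion rate that the protocol does not give.

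A reader might also infer that the plan lacks any handling of missed outcome prompts and is biased because answering t_n+1 may depend on whether a component was just delivered. Handling of missed prompts and completion by condition are details commonly left to a statistical analysis plan, which is not shown, so their absence cannot be held against this article. The MRT model already includes condition and negative affect at t_n. If missingness depends only on those, a likelihood-based fit accommodates it. The mixed model does not, however, restore power for moments whose dependent variable is missing.

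**Conclusion.** The point holds as a limit on a stated figure. The 80% MRT power for d=0.15 is correct only if the proximal outcome is observed after essentially every completed prompt, and it has almost no margin: about 5% loss of outcomes at ρ=0.85 and about 1% at 6:1 use it up. If t_n+1 is the next scheduled prompt, power lies between 0.73 and 0.53 for assumed next-prompt completion of 80% down to 50%, and the detectable effect is about d=0.16 to 0.21. If t_n+1 is the next completed assessment at any lag, the 80% is largely untouched by this point, but it refers to an effect at longer and variable lags.

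These results rest on the constant-effect approximation, on the assumed values of c, and on a trigger rate of 100%.

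The consequence is minor. The sample size is set primarily by the recruitment objective, the MRT effects are to be explored, and no traffic light criterion in Table 1 uses an MRT result.

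**What to change.** Two short edits would settle it.

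- In the specific active ingredients paragraph under Statistical Analysis, state whether t_n+1 is the next scheduled prompt or the next completed assessment and, if the latter, whether it may fall on another day.
- In MRT Sample Size Calculation, restate the power or the detectable effect using joint completion of prompts n and n+1, with a range such as the one tabulated above. Alternatively, state plainly that the 80% assumes a fully observed outcome.

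A sensitivity analysis weighted for the probability of answering t_n+1 is optional. If done, MRT condition must be in the weight model, because any selection caused by delivering a component runs through it.

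The cost is a few sentences and possibly a less favourable power figure. Data collection is complete, so the edits serve interpretation; no participants or new data are needed.
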